**Methods:**

We will recruit adult patients with chronic liver disease from the emergency departments, in-patient admissions, and an ambulatory liver clinic of a multi-site quaternary health service in Melbourne, Australia. A total of 120 patients meeting EF-Clif criteria will be recruited to the ACLF arm, and 320 patients to the hepatic decompensation arm. Participants in each cohort will be randomised to the intervention arm, a 28-day multidisciplinary programme or to standard ambulatory care in a 1:1 ratio. The intervention arm includes access to nursing, pharmacy, physiotherapy, dietetics, social work, and neuropsychiatry clinicians. For the ACLF cohort, the primary outcome is 28-day mortality. For the hepatic decompensation cohort, the primary outcome is 30-day re-admission. Secondary outcomes assess changes in liver disease severity and quality of life. An interim analysis will be performed at 50% recruitment to consider early cessation of the trial if the intervention is superior to the control, as suggested in our feasibility study. A cost-effectiveness analysis will be performed. Patients will be followed up for 12 weeks from randomisation. Three exploratory subgroup analyses will be conducted by (a) source of referral, (b) unplanned hospitalisation, and (c) concurrent COVID-19. The trial has been registered with the Australian New Zealand Clinical Trials Registry.

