**Table 3 Tab3:**
[figure not shown]
Standard Protocol Items: Recommendations for Interventional Trials (SPIRIT) figure

t_1_ 28 days after allocation, t_2_^a^ week 6 follow-up, t_3_^b^ week 12 follow-up

^c^Changes in liver disease severity, quality of life, and cost-effectiveness compared to standard care

^d^(a) Source of referral, (b) re-enrolment after unplanned hospitalisation, (c) COVID-19, and (d) hepatic decompensation without ACLF

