**Fig. 1 Fig1:**
[figure not shown]
Patient journey map

**Table 5 Tab5:** Key time points and tasks for completion

	Day 1	28-day programme	Week 6	Week 12
Timeframe for completion	Within 3 days	Weekly	Within 7 days	Within 2 weeks
Tasks	Blood tests EQ-5D CLDQ	Blood tests Complex Care Liver Clinic	Blood tests DQ-5D CLDQ	Blood tests Complex Care Liver Clinic

Patients on the LivR Well programme will be remotely monitored in between clinic appointments through a custom-built app paired to a Bluetooth scale. Patient-reported outcome measures (PROMS) including quality of life, will be collected through a mobile phone text message link to the online surveys. Patients will also be able to access Lucy LiverBot, a custom-built artificial intelligence ChatBot for all disease-related questions. Quality of life assessments will be performed at day 1 and longitudinally at 6 weeks and 12 weeks from admission in both arms of the RCT. Two validated instruments will be used [EuroQol 5 Dimensions (EQ-5D) [25] and Chronic Liver Disease Questionnaire (CLDQ)] [26]. Outcomes from these assessments will guide the economic evaluation for a cost-effectiveness analysis. Adherence will be monitored through recording attendance at appointments, home visits and regular urinary ethyl glucuronide tests, a biomarker of alcohol consumption [27].

The comparator will be outpatient management in a ‘complex care liver clinic’, an ambulatory care clinic for patients with decompensated cirrhosis, promoting continuity of care by a gastroenterologist, hepatology nurse and pharmacist through regular face-to-face appointments. The control cohort will have no access to the additional allied health clinicians, technology aids or home visits through the LivR Well programme.

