#### Recruitment

Patients will be recruited from the following settings: (a) following an acute hospital admission, (b) directly from the emergency department if able to be discharged home or (c) from the complex liver care clinic if ACLF or decompensation develops. All patients will be assessed by a gastroenterologist and allied health clinicians prior to recruitment. A research assistant or Pharmacist Informatician will provide eligible patients with a Participant Information and Consent Form (PICF) (Appendix 4) and consent will be obtained by a sub-investigator. Patients will be reviewed and admitted to the programme on the day of enrolment. All patients receiving LivR Well will also be onboarded to a mobile application and provided with the requisite hardware and software. Participants will be discontinued from the trial if consent is withdrawn, or if a serious adverse event (as defined on page 9) or death occurs. All participants will be included in the intention-to-treat analysis. If patients are admitted to the hospital after enrolment but before completion, the 28-day programme can be re-started on discharge if the patient still meets eligibility criteria and at the discretion of the treating team.

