#### Screening and randomisation

Patients will be screened against inclusion and exclusion criteria at the time of diagnosis of ACLF or hepatic decompensation. Those who meet the criteria will be enrolled into the study and provided informed consent. These recruited patients will be randomised in a 1:1 ratio to either the LivR Well programme or to complex care liver clinic in the control arm. Participants will be computer randomised and informed of their allocation by the CLD nurse specialist prior to discharge or within 24 hours of obtaining informed consent. Patients from both study arms will be registered on the Virtual Hospital masterlog through the Microsoft Power Apps program. Due to the nature of the intervention, blinding of study participants or clinical staff administering the LivR Well programme will not be possible. However, outcome ascertainment for the primary outcome, as well as the health services utilisation secondary outcomes will be blinded. Furthermore, all data analyses will be undertaken in a blinded manner. The statistician will be blinded to the feasibility study data results and the treatment allocation of the RCT.

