#### Statistical analyses

The data analysis for the primary composite endpoint of death, referral for liver transplantation or 30-day readmission from the date of hospital discharge will be undertaken on an intention-to-treat basis. A 28-day mortality rate will be calculated from the date of randomisation. For the primary and other binary outcomes, chi-squared tests will be used to compare the intervention and control groups. Survival analyses will also be undertaken, with the generation of Kaplan-Meier curves and Cox regression analyses to derive (adjusted) hazard ratios. For continuous outcomes, t-tests or non-parametric equivalents (e.g., Mann-Whitney tests) will be applied to compare the intervention and comparator groups. A *p* value of 0.05 is considered significant and 95% confidence intervals will be reported for all effect estimates Three exploratory subgroup analyses are planned: (a) comparing groups by the source of referral—conducted to address bias created following randomisation whereby in-patients in the intervention arm may be discharged home earlier due to perceived safety with regular home visits compared to those in the control arm. This subgroup analysis will account for differences between those admitted from in-patient admission compared to the emergency department or the ambulatory liver clinic; (b) comparing groups by re-enrolment to LivR Well after drop out due to unplanned re-admission to hospital. Data from the first enrolment to LivR Well will be included in the primary outcomes on an intention-to-treat basis and (c) patients with COVID-19 at the time of referral. Analyses will be performed using Stata statistical software, version 16.1 for Mac (StataCorp, College Station, TX, USA).

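### Exploratory subgroup (b) is defined by re-enrolment to LivR Well, a post-randomisation event that only intervention patients can have, so it has no control counterpart

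*Protocol article*

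**What the plan says.** The protocol article describes subgroup (b) in three places.

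- Statistical analyses: "comparing groups by re-enrolment to LivR Well after drop out due to unplanned re-admission to hospital".
- Table 3, footnote d: "b) re-enrolment after unplanned hospitalisation", which is the same variable.
- Abstract, Methods: the three subgroups are "a) source of referral, (b) unplanned hospitalisation, and (c) concurrent COVID-19". Here (b) is hospitalisation, with no mention of re-enrolment.

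The Recruitment section sets out how re-enrolment arises. It applies "If patients are admitted to the hospital after enrolment but before completion", and then "the 28-day programme can be re-started on discharge if the patient still meets eligibility criteria and at the discretion of the treating team".

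Patients are "randomised in a 1:1 ratio to either the LivR Well programme or to complex care liver clinic in the control arm" (Screening and randomisation). On the comparator, Processes, interventions and comparisons states: "The control cohort will have no access to the additional allied health clinicians, technology aids or home visits through the LivR Well programme".

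Two further statements limit the consequences. Statistical analyses says, directly after (b), that the primary outcomes use data from the first LivR Well enrolment by intention to treat. The Discussion calls the subgroups exploratory, concedes in general terms that they may be biased, hard to interpret and underpowered, and suggests that the data might be used in a sensitivity analysis instead.

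**The concern.** A subgroup analysis asks whether the randomised effect differs between kinds of patient. The kinds must be fixed before randomisation, and both arms must be represented in each. Re-enrolment to LivR Well meets neither condition. It is decided after randomisation, in one arm, by a chain of events: readmission, discharge alive, continued eligibility and a decision by an unblinded treating team.

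What is at stake is how an exploratory result is read. Patients who restart have, by definition, survived a readmission. Intervention patients who do not restart have been stripped of many of their readmissions. Either group set against controls can show a large difference when the programme does nothing, and a favourable figure could be taken as support for a second course.

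**Working it through.** The article gives no figure for subgroup (b), so there is none to reproduce. The check is structural first, then illustrative.

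**1. Who can be in the re-enrolled stratum**

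- Timing: the triggering admission falls after enrolment (Recruitment), hence after randomisation.
- Arm: controls have no access to LivR Well (Processes, interventions and comparisons), so none can re-enrol.
- Result: controls in the stratum = 0, whatever the sample size. Neither a within-stratum treatment effect nor an interaction can be estimated.

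**2. How many intervention patients might be involved**

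Expected readmissions = number in the arm × readmission risk. A patient must be readmitted before re-enrolling, so this bounds the expected number of re-enrolments.

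- Decompensation, planned 17% (Sample size): 160 × 0.17 = 27.2, about 27.
- Decompensation, 34.4% (the health service's rate for ACLF admissions, Background): 160 × 0.344 = 55.0.
- ACLF, 18.75% (feasibility study, Background): 60 × 0.1875 = 11.25, about 11.

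**3. Size of the distortion in the decompensation cohort with no treatment effect**

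Let readmission risk be p in both arms, let a share q of readmitted LivR Well patients re-enrol, and ignore death. The values of q are assumptions. Readmission among LivR Well patients who do not re-enrol is p(1 − q)/(1 − pq).

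| p | q | LivR Well, not re-enrolled | Controls |
|---|---|---|---|
| 34.4% | 0.5 | 0.172/0.828 = 20.8% | 34.4% |
| 34.4% | 0.8 | 0.0688/0.7248 = 9.5% | 34.4% |
| 17% | 0.5 | 0.085/0.915 = 9.3% | 17% |
| 17% | 0.8 | 0.034/0.864 = 3.9% | 17% |

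Re-enrolled patients whose readmission fell inside the 30-day window have an event rate of 100%. A programme with no effect would thus look strongly protective in one stratum and useless in the other.

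**4. ACLF cohort with no treatment effect**

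Here the primary outcome is death, and the distortion is immortal time. A simulation of 2,000,000 patients used exponential death times (33.9% by day 28), independent exponential readmission times (34.4% by day 30) and an assumed mean readmission stay of 6 days, with q from 0.5 to 1. It gave 28-day mortality of about 14% in re-enrolled patients, 37% to 40% in LivR Well patients not re-enrolled, and 34% in controls. The true effect was nil throughout.

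**5. The Abstract's wording**

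If (b) means unplanned hospitalisation, both arms contribute patients. The stratum is still formed after randomisation, so its two arms need not be comparable. In the decompensation cohort, splitting by hospitalisation is close to splitting by the primary outcome, which would push the arms towards the same event rate within each stratum whatever the programme does.

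**The case against.** The strongest reply is that little depends on (b). The primary result is protected, because only first-enrolment data enter it by intention to treat. The subgroups are labelled exploratory, the Discussion concedes bias and low power, and no trial decision rests on them. This stands, and it limits the severity. It does not remove the defect. The exploratory label deals with power and multiplicity; it supplies no comparator. The Discussion does not name the missing control group, and its suggestion of a sensitivity analysis could carry the same comparison further.

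A second reply is that the article states no effect measure for (b), so it might mean only re-enrolled against other LivR Well patients. That is possible, although the parallel wording of subgroup (a), which is aimed at a difference between arms, points to a between-arm comparison. Read within the arm, (b) is a description and should be labelled as one.

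Three stronger inferences are tempting, and the document does not support them:

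- That re-enrolment biases the primary result. The first-enrolment rule excludes this.
- That 27 is the most patients the stratum could hold. It is an expected count at a planning rate.
- That every re-enrolled patient in the decompensation cohort has had the primary event. Statistical analyses counts readmission from hospital discharge, while the restart rule runs from enrolment, and patients recruited from the clinic may have no index discharge. The overlap is large but not certain to be complete.

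**Conclusion.** The concern holds, with limited severity. As worded in Statistical analyses and Table 3, subgroup (b) has no controls by design, and any comparison of its strata with controls is selected on readmission, survival to discharge and clinician choice. Under the Abstract's wording the one-arm problem disappears, but conditioning on a post-randomisation event remains.

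The absence of controls follows from the text alone. The sizes in steps 3 and 4 of the working are illustrations: they depend on the assumed q, the assumed stay, independent event times in the simulation and, in step 3, ignoring death.

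**What to change.** 1. Reconcile the Abstract, Table 3 footnote d and Statistical analyses so that (b) has one meaning.
2. Remove (b) as a between-group subgroup comparison, and do not carry it into the sensitivity analysis suggested in the Discussion.
3. Report the number of re-enrolled patients and their subsequent course descriptively, within the LivR Well arm only.
4. Keep any between-arm comparison of readmission as an outcome in all patients as randomised.

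These changes cost only wording.

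A comparison of all repeat admissions between arms is optional, because it answers a different question. It would need admissions to be followed to week 12 in both arms after a serious adverse event. That cannot be taken for granted: Recruitment discontinues participants after a serious adverse event, Adverse events counts hospitalisation as one, and Recruitment also allows a restart after admission. Those passages must be reconciled before such an analysis is added.

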#### Economic analysis

The economic analysis will examine the cost-effectiveness of the LivR Well programme compared to the less resource-intensive control arm and will include both health system and societal cost perspectives. The main output of interest is the incremental cost-effectiveness ratio (ICER) in terms of net costs per unit of health gain. Health gains will be measured in clinical outcomes, estimation of years of life gained, quality-adjusted life years (QALYs) gained and by collection of quality-of-life data. Net costs will comprise the differential costs of the LivR Well programme and usual care minus costs saved from reduction in downstream health service utilisation. All health economic analyses will be undertaken in accordance with recommended approaches such as 5% discounting of estimated future costs and health gains. To account for any uncertainty in the data inputs for health economic modelling, sensitivity and uncertainty analyses will be undertaken via Monte Carlo simulation [31].

#### Dissemination of trial results

Trial results will be disseminated to healthcare professionals and the public through publication in a peer-reviewed journal and presentation at national and/or international conferences. Results will be distributed to participants during post-trial follow-up in the liver clinic. There are no specific publication restrictions; however, a high-impact hepatology journal will be approached.

## Discussion

We will evaluate the feasibility, acceptability, safety, efficacy and cost-effectiveness of LivR Well, a 28-day multidisciplinary liver optimisation programme following hospital admission with ACLF or hepatic decompensation. The programme consists of regular home visits, weekly medical reviews and access to multi-disciplinary team (MDT) care including medical, nursing, pharmacy, dietetics, social work and physiotherapy. Our feasibility study of 32 patients found that the programme was safe, feasible and acceptable and demonstrated a mortality rate of 3% and a re-admission rate of 18.5%.

The single-centre RCT aims to evaluate the impact on mortality and re-admission rate as well as disease severity, quality of life and cost-effectiveness. We anticipate that these results will guide the application of the programme in our quaternary health service, in other similar services and potential adaptation for use in regional centres.

One of the key strengths of this intervention is the use of a MDT approach enabled by technology. The MDT approach has previously been demonstrated to reduce mortality and outcomes in other chronic diseases including heart failure and chronic obstructive pulmonary disease [32]. The additional contributing factors including psychosocial issues associated with alcohol and other substance use disorders that contribute to poor health outcomes in this population must be acknowledged and addressed. The holistic approach of existing chronic disease management strategies can be applied to this similarly complex cohort. A nurse-led chronic disease management programme was assessed by Wigg et al. [8] in 60 patients randomised to the intervention (n=40) or usual care (*n*=20), which did not demonstrate an improvement in hospital admission rates, disease severity or patient quality of life. However, that study was limited by the sample size and did not incorporate a MDT. Our study aims to further explore these outcomes using a MDT approach, the inclusion of patients during an acute deterioration and with a larger population.

We acknowledge limitations in this study design and the ways we have attempted to address these. The trial is unblinded by nature, which may influence decisions such as referral for liver transplantation, re-admission to and discharge from hospital, clinical decisions especially for the control group, and referral for other procedures eg elective surgery. The statewide liver transplantation unit is external to Monash Health therefore referrals for consideration of transplantation are made using the centre’s own criteria. The other decisions will be challenging to address the influence of knowledge of the allocation group, and as such we will include this in the discussion. Patients in the intervention group may be re-admitted to the hospital faster due to close follow up or conversely, patients in the control group may be re-admitted at a lower threshold due to the absence of home-based support.

The economic evaluation will be a cost-effectiveness analysis and is essential to guide health services to strategically invest in sustainable ambulatory care to reduce emergency presentations and improve healthcare-related quality of life. This is of particular importance in this population with a high healthcare system burden [33], re-admission [34], and mortality rates.

The subgroup analyses are considered ‘exploratory’ as we acknowledge the potential for bias and challenging interpretation of results. It is unlikely with our total sample sizes that the subgroups will be adequately powered to draw conclusions and therefore another consideration could be using these data in a sensitivity analysis.

### Trial status

Study protocol V15

The trial is open for recruitment from January 10, 2022. The approximate date for completion of recruitment is March 2023

## Data Availability

On completion of the trial, the final datasets generated and/or analysed will be available from the corresponding author on request. Access to the final datasets will be in accordance with governance policies, Good Clinical Practice guidelines and ethics committee policies. The research team will be accountable to an independent data and safety monitoring board throughout the study. Any protocol amendments will be communicated to all relevant parties.

## Abbreviations

ACLF: Acute-on-chronic liver failure
CLD: Chronic liver disease
CLDQ: Chronic Liver Disease Questionnaire
EQ-5D: Euro Quality of Life 5 Dimension
FiO_2_: Fraction of inspired oxygen
FRAT: Falls Risk Assessment Tool
HGS: Handgrip strength
HITH: Hospital in the Home
INR: International Normalized Ratio
MAP: Mean arterial pressure
MUST: Malnutrition Universal Screening Tool
MDT: Multidisciplinary team
MELD: Model for End-Stage Liver Disease
PaO_2_: Partial pressure of arterial oxygen
PI: Primary investigator
PICF: Patient informed consent form
PROM: Patient-reported outcome measures
RCT: Randomised controlled trial
SAE: Serious adverse event
SPIRIT: Standard Protocol Items: Recommendations for Interventional Trials
SpO_2_: Pulse oximetric saturation
WHO: World Health Organization
